### FDG-PET/CT imaging

Increased glycolysis is one of the hallmarks of cancer. FDG, an analogue of glucose labeled with a positron emitting isotope of Fluor (F^18^), is actively taken up in cancer cells of many tumor types. The positrons emitted by the FDG are detected by a dedicated camera, enabling the visualization of cellular glycolytic activity [37]. Serial FDG PET-CT consists of performing a scan at baseline (day 1) and after 2 weeks (day 15). The two PET-CTs need to be performed in strictly identical and standardized conditions.

The practical guidelines for FDG PET-CT imaging (activity injected; acquisition timing; processing; image analysis; PET-CT data form input) are specified in the Standard Procedure Imaging Manual (SPIM) for PET-CT, following as closely as possible the EANM procedure guidelines for tumor PET imaging [38]. Measurement of several FDG PET-CT metabolic parameters such as SUV, FTV and TLG for analysis will be documented. To respect FDG PET quantifications, an ultra-low dose CT (approx 1 mSv) will be performed to correct the metabolic images.

### Magnetic resonance imaging

The technical protocol will include T1 and T2 weighted images without contrast and a diffusion-weighted sequence with area under the curve calculation made on 2 B values with the first being superior to 150 ms to eliminate the fast component (microvessel-related) in order to get an expression of the true water diffusion properties of the tissue. The second B value will range between 800 and 1200 ms. The duration of this non-contrast imaging examination is about 20 minutes per patient. Volumetric, voxel-based vADC values will be computed with dedicated software at the sponsor institution (Institut Jules Bordet). ROI-based mean ADC value at the larger non-necrotic part of the lesion will also be determined.

### Genomic alterations

To detect tumor-specific alterations in plasma DNA via NGS technology, blood samples for plasma preparation will be collected at baseline (2 × 9 mL) and at 2 weeks (2 × 9 mL) after the start of the study (see Figure 1). An extra 9 mL whole blood sample will be collected at baseline in order to distinguish somatic from germline mutations. Extracted DNA samples will be used for further analysis using NGS. DNA will also be extracted from previously available tumor biopsies of the included patients in order to identify and quantify tumor-specific alterations.

### Circulating tumor cells

For CTC quantification, a 9 mL peripheral blood sample from each patient will be collected and sent at room temperature to the laboratory responsible for CTC detection at baseline and at 2 weeks after the start of the study (see Figure 1). These blood samples will be processed using Veridex, LLC,CellSearch®, and the identification and counting of CTCs will be performed with the CellSpotter™Analyzer, which is a semi-automated fluorescence-based microscopy system that permits computer-generated reconstruction of cellular images.

The laboratory investigators will be blinded to the clinical status of the patients.

### Follow-up

Follow-up procedures, performed every 2 months after the second PET-CT assessment, will include physical examination, vital signs and ECOG performance status, laboratory tests and diffusion-weighted MRI.

### Statistical considerations

Our primary analysis will consist of the assessment of the prognostic value of TMPI (evolution of the tumor FDG uptake from baseline to 2 weeks later) on OS. The patients will be divided into 2 groups using the observed median as threshold. The primary comparison will be done using Kaplan-Meier estimates of OS distributions and comparison using the log rank test (2-sided level of 5%). Based on published data from our team [19], we believe that a HR of .40 favoring patients with slow growing tumors could be expected and would have a clinically pertinent value. In order to detect such a HR if true, with a power of 80%, we need to have complete follow-up (observation until death) for 37 patients. Time zero for measuring survival will be the day of the second FDG PET-CT assessment.

Getting this number of events, assuming a median survival of 4 months for the overall population (i.e., we anticipate a median of 5.7 months for the patients with slow growing tumors and 2.3 months for the other patients), should be feasible with an accrual of 3 to 4 patients per month and registration of 47 patients with a FDG PET-CT evaluation after 2 weeks. An increase in sample size to 53 patients should compensate for the fact that not all patients will have a second FDG PET-CT assessment or at least one metabolic measurable lesion.

Analysis of the primary objective will be conducted using data from the patients who undergo the 2 FDG PET-CT evaluations.

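### Minor: 37 deaths give about 77% power at HR 0.40, slightly short of the stated 80%, and the overall median of 4 months does not fit the two group medians

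*Protocol article*

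**What the plan says.** All of the following is in the protocol article under Statistical considerations.

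- **Groups:** "The patients will be divided into 2 groups using the observed median as threshold", so the two groups are of nearly equal size.
- **Test:** a log-rank comparison of overall survival at the two-sided 5% level.
- **Effect:** "we believe that a HR of .40 favoring patients with slow growing tumors could be expected".
- **Events and power:** "with a power of 80%, we need to have complete follow-up (observation until death) for 37 patients".
- **Patients and entry:** the deaths are expected from "an accrual of 3 to 4 patients per month and registration of 47 patients with a FDG PET-CT evaluation after 2 weeks". The increase to 53 registrations covers patients without a second scan or a measurable lesion, and has no bearing on power at a given number of deaths.
- **Survival:** the projection is made "assuming a median survival of 4 months for the overall population", and explained by the words "we anticipate a median of 5.7 months for the patients with slow growing tumors and 2.3 months for the other patients".

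The article names neither the formula behind the 37 deaths nor a survival distribution.

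**The concern.** Two things do not fit.

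First, the usual log-rank event formula gives slightly more than 37 deaths, and required events are normally rounded up. That formula is also a large-sample approximation for modest effects. At HR 0.40 the fast-growing group dies out early, the later risk sets become unbalanced, and each late death carries less information than the formula assumes. With fewer than 40 deaths this can cost a few points of power. This is the only primary test, so its stated power should describe the test that will be run.

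Second, 4 months is the arithmetic mean of 5.7 and 2.3. The median of a pooled population is not in general the mean of the two group medians, so the overall figure and the group figures may not describe the same population.

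**Working it through.** **Inputs, all from Statistical considerations:** HR 0.40; two-sided alpha 0.05 (z = 1.960); power 80% (z = 0.842); median split, so 1:1; 37 deaths; 47 evaluable patients; 3 to 4 patients a month; group medians 5.7 and 2.3 months.

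**1. Reproducing the plan's figure (Schoenfeld, 1:1).**

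Events = 4(1.960 + 0.842)² / (ln 0.40)² = 31.40 / 0.8396 = 37.39.

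This matches the stated 37 if rounded down; rounding up gives 38. Power at d deaths is Φ(√d · |ln HR| / 2 − 1.960):

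- 37 deaths, HR 0.40: Φ(2.787 − 1.960) = Φ(0.827) = 79.6%
- 38 deaths, HR 0.40: 80.6%
- 37 deaths, HR 2.3/5.7 = 0.404 (the printed medians): 78.8%

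Rounding down therefore costs 0.4 points against the 80% target.

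**2. A second formula for comparison (Freedman).**

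Events = (1.960 + 0.842)² × (1.40/0.60)² = 7.849 × 5.444 = 42.7, so 43. Power at 37 deaths by this formula is 74.1%.

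**3. Simulating the planned test.** Added assumptions: exponential survival, uniform random entry, and analysis at the calendar time of the d-th death. There were 47 patients, with 100,000 trials for each split (24/23 and 23/24), averaged. The Monte Carlo standard error is about 0.1 point. HR is exactly 0.40 (medians 5.75 and 2.3).

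| Deaths | Entry 3 a month | Entry 4 a month | All enter together |
|---|---|---|---|
| 37 | 77.2% | 77.5% | 76.4% |
| 38 | 78.5% | 78.6% | 77.5% |
| 39 | 79.3% | 79.7% | 78.5% |
| 40 | 80.3% | 80.6% | 79.8% |
| 41 | 81.5% | 81.7% | 80.9% |

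Evenly spaced entry at 3 to 4 a month gives 76.9–77.9% at 37 deaths, so the entry pattern matters little. With the printed medians 5.7 and 2.3, power at 37 deaths is 76.1–76.8%; at 3.5 patients a month it is 79.6% at 40 deaths and 80.5% at 41. The simulated size under no effect at 37 deaths is about 5.4%, so a conservative test does not explain the shortfall.

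**4. Time cost of more deaths.** Mean time from the start of accrual, averaged over the two splits:

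- at 3 a month: 18.0 months to 37 deaths, 20.2 to 40, 21.2 to 41
- at 4 a month: 15.3, 17.6 and 18.6 months

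The extra wait is about 2.2 months for 40 deaths and 3.2 months for 41.

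**5. The medians.** For a 50:50 mixture of exponentials the pooled median t solves 0.5 · 2^(−t/5.7) + 0.5 · 2^(−t/2.3) = 0.5, which gives t = 3.51 months. At t = 4 the left side is 0.5 × 0.615 + 0.5 × 0.300 = 0.457, so more than half would already have died. The arithmetic mean (5.7 + 2.3)/2 is exactly 4. Scaling both medians by 4/3.51 = 1.14 gives 6.5 and 2.6 months, which keeps the ratio at 0.40 and has a pooled median of 4.

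**The case against.** The strongest reply is that nothing was miscalculated. Schoenfeld's formula is standard, its 79.6% at 37 deaths rounds to the stated 80%, and preferring simulation is a choice of method. That stands as far as it goes: it explains where 37 came from and rules out calling the sample size wrong. It does not give the log-rank test 80% power in this design.

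A second reply is that the article presents 37 as a number needed and does not say that the analysis will be cut at the 37th death. This also stands. With 40 or 41 deaths among the same patients the stated power is reached. Still, the text ties 80% to 37 deaths, and that is the pair to correct.

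A third reply is that the gap is small beside the uncertainty in the effect. By Schoenfeld, power at 37 deaths is 77.4% at HR 0.41 and about 68% at HR 0.45. This is fair, and it is why the point is minor.

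Stronger readings are tempting but unsupported:

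- A reader might infer from Freedman's formula that 43 deaths are required and that power is only 74%. The simulation shows this formula to be conservative here, since 80% is reached at 40–41 deaths.
- A reader might infer that a non-significant result would be seriously over-interpreted. Three points of power do not carry that.
- A reader might infer that the wrong overall median threatens the event target. If the group medians hold, deaths come somewhat sooner than a pooled median of 4 months suggests, so feasibility is not weakened.

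**Conclusion.** The point holds as a minor one. At 37 deaths among 47 patients the planned test has about 77% power for HR 0.40, and 76–77% with the printed medians, which imply HR 0.404. The type II error is about 23%, against the 20% stated. Of the gap, 0.4 points come from rounding 37.39 down; the rest is the error of a standard large-sample approximation at a strong effect with few events. The simulated figures rest on exponential survival, entry at 3 to 4 a month and a cut at the 37th death, none of which except the entry rate is stated in the article.

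The overall median of 4 months is inconsistent with group medians of 5.7 and 2.3 months, whose mixture median under exponential survival is 3.5. The medians do not enter the event formula, so this affects only the projected timing of deaths.

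**What to change.** Choose one of two changes for the power statement:

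1. Keep 37 deaths and restate the power as about 77%, naming the method and assumptions. This is a change of wording only.
2. Keep the 47 evaluable patients and run the primary log-rank test at 40–41 deaths, for about 80–81% power. With the printed medians, 41 is the safer count. The cost is about 2–3 more months of survival follow-up and no extra patients.

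A target of 43 deaths is not needed.

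In either case, make the medians agree: give the overall median as 3.5 months, or keep 4 months and rescale the group medians to about 6.5 and 2.6 months. Then update the projected date of the analysis. This costs a line of text.

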## Ethical considerations

### Patient protection

The principal investigator ensures that this study conforms to the Declaration of Helsinki (available at http://www.wma.net/en/30publications/10policies/b3/) or the laws and regulations of the country, whichever provides the greatest protection of the patient.

The study follows the International Conference on Harmonization E 6 (R1) Guideline for Good Clinical Practice, reference number CPMP/ICH/135/95 (available at http://www.ich.org/fileadmin/Public_Web_Site/ICH_Products/Guidelines/Efficacy/E6_R1/Step4/E6_R1__Guideline.pdf).

The competent ethics committee of the Institut Jules Bordet approved the protocol, as required by applicable national legislation.

## Discussion

Tumor aggressiveness is one of the major determinants of patient outcome in advanced disease. Despite its importance, supported by findings reported in the literature of extreme outcomes for patients with mCRC treated with chemotherapy, no objective tool allows clinicians to base treatment decisions on this factor.

The CORIOLAN study will characterize TMPI using FDG-PET-based metabolic imaging of patients with chemorefractory mCRC during a period of time without treatment. Results will be correlated to other assessment tools like DW-MRI, CTCs and circulating DNA, with the aim to provide usable tools in daily practice and in clinical studies in the future.

## Abbreviations

ADC: Apparent diffusion coefficient; CTCs: Circulating tumor cells; DW-MRI: Diffusion-weighted magnetic resonance imaging; DWI: Diffusion-weighted imaging; EANM: European association of nuclear medicine; FDG-PET-CT: Fluoro deoxy glucose-positron emission tomography/computed tomography; FTV: Functional tumor volume; HR: Hazard ratio; mCRC: Metastatic colorectal cancer; MRI: Magnetic resonance imaging; NGS: Next generation sequencing; OS: Overall survival; PFS: Progression free survival; RECIST: Response evaluation criteria in solid tumor; ROI: Region of interest; SPIM: Standard procedures imaging manual; SUV: Standardized uptake value; TLG: Total lesion glycolysis; TMPI: Tumoral metabolic progression index; TTP: Time to progression; vADC: Volumetric evaluation of apparent diffusion coefficient.
